### **7.3 Supply, packaging and labelling**

All vaccines will be stored at 4°C. Each vial of study drug will have a pre-printed label including the following information: study number, bulk batch number, and volume. A space is also provided for the person administering the drug to enter the individual's ID number and initials at the time of administration. The vial will be labelled for Clinical Trial Use Only.

### **7.4 Preparation**

A minimum of 30 minutes before administration the vaccine will be transferred from 4°C storage to room temperature for temperature equilibration. Standard TIV will be supplied in a pre-packaged syringe with needle as supplied by the manufacturer. For subjects receiving the adjuvanted vaccine, the adjuvant will be supplied and mixed with vaccine as per the vaccine administration SOP. The vaccine is mixed by repeated inversion before the complete contents of the vial are aspirated into either a new 1ml syringe or the needleless injector device disposable cartridge. The formulated vaccine can be kept at room temperature for 8 hours. Before administration, the adjuvanted vaccine syringe/cartridge should be inverted a number of times to ensure even mixing of

the adjuvant. Standard influenza vaccine is a clear solution whereas the vaccine containing adjuvant is a cloudy white colour.

### **7.5 Administration of injection**

The total dose will be given as a single injection into or over the deltoid muscle using a suitable disposable sterile syringe mounted with a 25-27G needle if in the standard syringe adjuvanted TIV groups, pre-packaged syringe and fixed needle if in the standard syringe TIV alone group, or the needleless applicator if in needleless injector groups.

### **7.6 Emergency Procedures**

For vaccines the incidence of anaphylactic reactions are negligible, but emergency equipment must be available.

In case of anaphylactic shock the SA Health Anaphylaxis – Management Guidelines CC1.255 will be followed, as attached

Cases of anaphylactic shock must be reported as SAEs. Treatment should be permanently discontinued should such an event occur.

### **7.7 Storage, issue, return and accountability of study drugs**

#### **7.7.1 Storage**

Study vaccines must be stored at a temperature of 4°C. Freezing may destroy the effectiveness of the vaccine. The study vaccines and adjuvant must be stored in a secure location at the investigator's site and may be dispensed only by the investigator or by a member of staff specifically authorised by the investigator.

#### **7.7.2 Issue and return of study vaccines and adjuvant**

The dispensing of the study vaccine to the investigators and subsequent administration to study subjects will be recorded on the drug accountability form and accurate accounting will be given to the monitor at each monitoring visit. Unused study vaccines must not be discarded or used for any purpose other than the present study.

#### **7.7.3 Accountability of study vaccine**

All vaccine supplies for this study should be retained in a safe secure place at all times during the study. The investigational product(s) should be administered by the investigator, or by a qualified individual under the investigator's supervision. An up to date vaccine inventory/dispensing record must be maintained. The individual's ID number and initials should be written on each vial just before it is administered to an individual. The empty or partially empty vials must then be stored, so that the vials administered to each individual can be verified by the study monitor. After completion of the study, all unused material must be accounted for. If the investigator or hospital pharmacist destroys the supplies, written documentation is mandatory. The record must include the following: who destroyed the supplies, the identity and quantity of what was destroyed, and the method and date of destruction. All drug supplies must be accounted for. At the end of the study, a copy of the vaccine inventory/dispensing record should be stored and a copy kept in the investigator's study file. The investigator is responsible for the vaccine supplies.

### **7.8 Criteria for dose modification, dose escalation or vaccine discontinuation**

### **7.8.1 Dose modification**

The dose administered should always be in accordance with the protocol. If a dose other than that shown in the protocol is administered then this should be recorded as a protocol violation.

### **7.8.2 Vaccine discontinuation**

Individuals who have had past history of potential vaccine reactions will be assessed by the investigator, who will decide whether any past potential vaccine-related side are sufficiently minimal to allow the subsequent administration to proceed.

### **7.8.3 Dose limiting toxicities**

Toxicities that must be considered as serious adverse events (SAEs) are:

1. Grade II to IV allergic reactions.
2. Grade IV neutropenia.
3. Grade IV thrombocytopenia.
4. Grade III to IV hypotension.
5. Grade III to IV dyspnea.
6. Occurrence of autoimmune disease.
7. Any Grade IV toxicity (except fever and flu-like symptoms which can be treated with paracetamol).
8. Recurring Grade III toxicities.

## **8. STUDY PROCEDURES AND EVALUATIONS**

### **8.1 Assessment periods**

One immunisation will be performed on Day 0 (Visit 1). Although the final study visit takes place 4 weeks after immunization, the total follow up period may be up to 12 months with a provision for a telephone call to the subject during this period to ascertain any new medical events that might have occurred during this interval.

### **8.2 Screening procedures**

Only subjects who fulfil the inclusion and exclusion criteria, and for whom written informed consent has been obtained, will be eligible for enrolment into the study, and consent must be obtained before any screening procedures are undertaken. Screening of individuals should take place within 28 days prior to the start of treatment. At the time of screening the following assessments/procedures will be performed:

1. Inclusion and exclusion criteria.
2. Written informed consent.
3. Demographic data (sex, race, date of birth).
4. Pregnancy test (if applicable)
5. Medical history, vaccination history, concurrent illnesses including details of primary diagnosis and previous treatments.
6. Physical examination.
7. Vital signs (supine blood pressure, heart rate, temperature).
8. Body weight and height.
9. Blood sample for influenza antibody and T-cell assessment.

### **8.3 Randomisation**

Study participants will be randomized to one of the treatment groups in the order of their enrolment in accordance with a predetermined balanced randomization protocol.

#### **8.4 Prior to treatment procedures**

The assessments that should be conducted at the visits are summarised in the Schedule of Assessments. Details of the evaluations are given below:

1. Physical evaluation.
2. History and concomitant medication.
3. Blood sample for baseline influenza antibody and T-cells before vaccine administration

#### **8.5 Follow-up**

The assessments that should be conducted at these visits are given in the Schedule of Assessments. The following evaluations will be performed.

1. Vital signs (blood pressure, heart rate, temperature).
2. Inspection of immunization site
3. Blood sample for influenza antibodies and T-cell responses and safety tests where indicated.
4. Adverse event history.

#### **8.6 Early termination**

At early termination of the study due to excess adverse events or any other reason the following procedures/tests will be performed.

1. Physical examination and vital signs (blood pressure, heart rate, temperature).
2. Blood sample for haematology and biochemistry (where indicated).
3. Blood sample for influenza antibodies and T-cell responses.
4. Recording of adverse events.

#### **8.7 Observations and measurements: Assessment for treatment effects**

##### **8.7.1 Medical history**

Information obtained will include history of underlying disease and concurrent illnesses (including the date of onset, if known), concomitant medication, vaccination history during the last 5 years before entry into the study and surgical procedures.

##### **8.7.2 Laboratory assessments**

##### **Local and central laboratory analyses**

##### **Routine laboratory tests**

Haematology and blood chemistry may be performed on selected subjects at discretion of the Investigator. Haematology assessment may include complete blood count including differential and platelet count, haemoglobin and haematocrit, ESR and coagulation studies. Biochemistry may include glucose, blood urea nitrogen, sodium, potassium, bicarbonate, chloride, creatinine, alkaline phosphatase, gamma-glutamyl transpeptidase (GGT), total bilirubin, aspartate transaminase (ASAT), alanine transaminase (ALAT), calcium, inorganic phosphorous, albumin, total protein and uric acid, rheumatoid factor and anti-nuclear antibodies, total haemolytic complement, C reactive protein, C3 and C4.

**Immune response assays.**

Blood samples will be drawn for the evaluation of influenza antibody titres of all the individuals immediately prior to immunization, and 7 days and 4 weeks post immunization. Those subjects who consent to be in the Substudy will have blood taken weekly for 4 weeks post-immunisation for analysis of B- and T-cell responses to influenza and control antigens.

**9. STATISTICAL METHODOLOGY AND ANALYSIS****9.1 Evaluations****9.1.1 Primary variables**

- (a) Antibody responses to each vaccine serotype as assessed by TGA criteria
- (b) Frequency and severity of SAE and AE including laboratory safety assessments.

**9.1.2 Secondary variables**

- (a) Injection tolerability and acceptability scores by questionnaire and visual analogue scales
- (b) Measurement of B and T-cell responses to influenza antigens
- (c) Gene expression changes correlating with vaccine outcomes (immunogenicity and/or reactogenicity)

**9.2. Description of individual groups for analysis****9.2.1 Safety population**

All enrolled individuals who received at least one dose of treatment will be included in the safety population.

**9.2.2 Per-protocol population (PPP)**

All individuals who received at least one dose of treatment and who provided baseline and at least one post-baseline measurement for influenza antibodies will be included in the per-protocol population.

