## **2. STUDY OBJECTIVES**

### **2.1 Primary Endpoints:**

- Seroconversion and seroprotection rates and mean GMT increases in haemagglutination inhibition titres 21-28 days post-immunisation for each of the three included vaccine strains

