### **5.3 Study Visit Window**

Scheduled Vaccination and Follow up Visits will be treated as within the study protocol, if performed plus or minus 7 days from the study day specified in the protocol. If a subject has a fever at a Vaccination Visit, then the Visit can be rescheduled by up to four weeks without recording a protocol violation.

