**9.4 Efficacy analysis**

All continuous data will be described by means of summary statistics: N, mean, standard deviation, minimum, median and maximum and 95% confidence intervals. Categorical variables will be presented using the number of observations (N), frequencies (%) and missing data.

The efficacy variables will be described by adequate methods in tables by visit and treatment group. The change from baseline to endpoint (if necessary defined as the last

value carried forward) will also be described by summary statistics. Influenza-specific antibody titres (IgM, IgG, IgG1-4, haemagglutinin inhibition (HI) titre) will be analysed by calculating changes from the background pre-immune serum readings.

All individuals with at least one post-baseline measurement for efficacy will be included in the efficacy population. The analysis will include listings of objective response according to currently pertaining TGA influenza vaccine criteria, (e.g. seroconversion = four fold increase in HI over baseline, seroprotection = post-immunisation HI of 1:40 or greater; potency = fold increase in HI geometric mean titres (GMT). GMT and 95% confidence intervals will be estimated pre- and post-immunisation and compared across groups by ANOVA. The proportion of each vaccine group achieving seroconversion or seroprotection will be compared by Fisher's exact test.

An efficacy analysis to identify differences in treatment response between unadjuvanted and adjuvanted TIV groups and between needle and needless injector groups will be performed on the complete PPP irrespective of age. Additional subgroup efficacy analyses to identify significant differences in treatment response between unadjuvanted and adjuvanted TIV groups and between needle and needless injector groups will be performed stratifying subjects by age.

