### **9.7 Sample size estimation**

The study population will comprise up to 400 subjects 18 years and older, who fulfil the inclusion criteria, and do not meet any of the exclusion criteria who will be randomised into 6 groups of 65 subjects per group. The TGA based on long standing experience with influenza vaccines requires a minimum group size of 50 subjects per group for assessment of influenza vaccine antibody responses for vaccine release purposes. Therefore, rather than using a power calculation based on our own limited assumptions, we have instead relied upon this TGA requirement as our guide in designing the group size for this study, further allowing for a 20% drop out rate for subjects failing to attend for the final blood sample, thereby ensuring we meet the TGA minimum group size.

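### The efficacy set and the carry-forward rule let a Day 7 HI titre stand in for the 21-28 day primary endpoint, and the visit window does not match that endpoint

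*Protocol*

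**What the plan says.** - **Endpoint.** Protocol section 2.1 makes the primary endpoint seroconversion, seroprotection and "mean GMT increases in haemagglutination inhibition titres 21-28 days post-immunisation for each of the three included vaccine strains".
- **Sampling.** Section 8.7.2 (Immune response assays) takes "titres of all the individuals immediately prior to immunization, and 7 days and 4 weeks post immunization". The Day 7 entry in section 4.1.1, however, describes that blood as being for plasmablasts only.
- **Efficacy set.** Section 9.2.2 states that dosed individuals who "provided baseline and at least one post-baseline measurement for influenza antibodies will be included in the per-protocol population". Section 9.3 runs efficacy on this set and has protocol violations listed by patient, with no exclusion following from them. Section 9.4 then defines a second efficacy population by any one post-baseline value.
- **Missing endpoint.** Section 9.4 reads "The change from baseline to endpoint (if necessary defined as the last" and continues on the next line with carry-forward of that value. Its definitions of seroconversion (fourfold rise) and seroprotection (HI of at least 1:40) name no day.
- **Window.** Section 5.3 treats a visit as within protocol "if performed plus or minus 7 days from the study day specified in the protocol".
- **Expected loss.** Section 9.7 allows for a "20% drop out rate for subjects failing to attend for the final blood sample".

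**The concern.** Each of these provisions looks routine alone. Read together, they leave the primary endpoint without a fixed time. A subject who gives blood at baseline and Day 7 and then misses the final visit belongs to the efficacy set. Nothing in the protocol stops that subject's Day 7 titre from being counted as the 21-28 day result. If the antibody response is still developing at Day 7, the reported seroconversion rate, seroprotection rate and GMT rise mix two time points in a proportion set by attendance.

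Two related faults affect the same endpoint. A set labelled per-protocol that removes no violators will be read as something it is not. And a final sample taken in the fifth week is valid under section 5.3 but lies outside the endpoint in section 2.1.

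What is at stake is whether each arm is judged fairly against the TGA criteria, and whether the comparison of adjuvanted with unadjuvanted vaccine is free of an artefact of missing visits.

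**Working it through.** **1. The plan's own figure.** Inputs from section 9.7: minimum 50 per group, 20% loss of the final sample, 65 per group, 6 groups.

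- Required: 50 / (1 - 0.20) = 62.5, so 63. The stated 65 is consistent with this.
- Observed final samples: 65 x 0.80 = 52, which is at least 50.
- Total: 6 x 65 = 390, within the limit of 400.
- Most subjects per group who could carry a Day 7 value: 65 - 52 = 13.

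The group size therefore already assumes that the final sample is missing for these subjects. Carry-forward is not needed to reach it.

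**2. Windows.** Inputs from sections 2.1, 4.1.1 and 5.3.

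- Final visit: 28 - 7 to 28 + 7 = Days 21-35. The endpoint covers Days 21-28, so Days 29-35 are valid for the visit but not for the endpoint.
- Day 7 visit: 7 - 7 to 7 + 7 = Days 0-14.

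This step needs no assumption.

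**3. Effect on one arm.** Let f be the share of the analysis set filled from Day 7, and p28 and p7 the response rates on the two days. Assume that subjects who miss the final visit respond like the others. Then:

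reported rate = (1 - f) x p28 + f x p7, so shift = -f x (p28 - p7).

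The protocol gives neither p28 nor p7. Assume p28 = 70% and p7 = 10% to 40%.

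| f | p7 | Reported rate | Shift |
|---|---|---|---|
| 20% | 10% | 0.80 x 70 + 0.20 x 10 = 58% | -12 points |
| 20% | 40% | 0.80 x 70 + 0.20 x 40 = 64% | -6 points |
| 5% | 10% | 0.95 x 70 + 0.05 x 10 = 67% | -3 points |
| 5% | 40% | 0.95 x 70 + 0.05 x 40 = 68.5% | -1.5 points |

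If p7 equals p28, the shift is zero.

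For the GMT fold rise g, the mixture is on the log scale: log g = (1 - f) log g28 + f log g7. With f = 20% and an assumed g28 = 4, a Day 7 rise of 1 gives 4^0.8 = 3.03 (24% lower). A Day 7 rise of 2 gives 4^0.8 x 2^0.2 = 3.48 (13% lower).

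**4. Effect between arms.** All rates are assumed, with f = 20% in both arms.

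| True Day 28 rates | Day 7 rates | Reported rates | True difference | Reported difference |
|---|---|---|---|---|
| 60% v 75% | 30% v 30% | 54% v 66% | 15 | 12 |
| 60% v 75% | 30% v 45% | 54% v 69% | 15 | 15 |
| 60% v 75% | 20% v 50% | 52% v 70% | 15 | 18 |
| 60% v 60% | 20% v 50% | 52% v 58% | 0 | 6 |

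Unequal loss acts in the same way. With 70% at Day 28 in both arms, the same Day 7 rate of 10-40% in both, and 15% v 25% filled, the false difference is (0.25 - 0.15) x (70 - p7) = 3 to 6 points.

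**The case against.** The strongest reply is that section 9.4 never says the Fisher tests use carried-forward values. It attaches the rule, conditionally, to a descriptive summary of change from baseline. It also tabulates efficacy by visit and shows missing data for categorical variables, and section 9.3 calls the analysis descriptive. This is a fair limit. A reader might infer that the plan prescribes Day 7 values for the seroconversion test, and the text does not say so. What stands is that seroconversion is itself a change from baseline, its definition has no day, and the set admits Day 7-only subjects. The substitution is open, though not ordered.

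Second, section 4.1.1 reserves the Day 7 blood for plasmablasts. If HI is not run on it, the mechanism disappears for most subjects. But section 8.7.2 states the opposite for everyone, so the conflict needs resolving and cannot be assumed away.

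Third, four further readings are tempting and unsupported:

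- **The bias is necessarily downward.** That requires Day 7 responses below Day 28 responses, for which the protocol gives no figure. Keeping violators has no fixed direction of effect either.
- **20% of values will be filled.** That figure is a planning allowance. Subjects lost before Day 7 have no post-baseline titre and are outside the set.
- **The seven-day window worsens carry-forward.** A Day 7 visit held late would lie nearer the developed response and could shrink the shift. The Days 29-35 mismatch is a separate fault.
- **A substudy Day 21 titre competes for the endpoint.** Sections 4.1.1 and 8.7.2 assign those bloods to B- and T-cell work and show no HI measurement on them.

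**Conclusion.** The point holds as a gap in the rules for the primary endpoint. Sections 8.7.2, 9.2.2 and 9.4 together permit a Day 7 HI titre to replace the 21-28 day value. The per-protocol label is wrong for a set without exclusions, and sections 2.1 and 5.3 disagree about Days 29-35. The last two statements rest on the text alone.

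The size is conditional. It assumes that HI is measured at Day 7, that carry-forward is applied to the HI endpoints, and that Day 7 responses are lower. With the assumed rates in the working, each arm's seroconversion rate is then 6-12 points too low at the upper bound of 20% filled and 1.5-3 points too low at 5%. For the adjuvant comparison the distortion can shrink, enlarge, create or leave unchanged a difference, so it cannot be called conservative.

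**What to change.** 1. Delete last value carried forward for the HI endpoints in section 9.4.
2. Base seroconversion, seroprotection and GMT rise on an observed HI titre from the final (Day 28) visit. State one acceptance window and use it in both sections 2.1 and 5.3.
3. Merge the PPP and the efficacy population into one set named for what it is, such as a modified full analysis set. Add a sensitivity analysis that excludes the violations listed in section 9.3.
4. Reconcile sections 4.1.1 and 8.7.2 on whether HI is measured at Day 7.

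The cost is wording, plus the loss from the primary analysis of subjects without a valid final sample. At the plan's own 20% loss, 52 of 65 per group remain, against a stated minimum of 50. The margin is only 2 per group, so the agreed window should not be so narrow that it discards many attended final visits.

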**9.3 Statistical analysis**

A descriptive analysis will be performed. All variables will be analysed descriptively. The safety analysis will be performed for the safety population. The efficacy analysis will be performed for the PPP population.

Protocol violations will be listed by patient. Protocol violations include the following:

- (a) Non-compliance of the inclusion and exclusion criteria.
- (b) Non-permitted concomitant medication
- (c) Scheduled visit occurring outside of visit window

**9.4 Efficacy analysis**

All continuous data will be described by means of summary statistics: N, mean, standard deviation, minimum, median and maximum and 95% confidence intervals. Categorical variables will be presented using the number of observations (N), frequencies (%) and missing data.

The efficacy variables will be described by adequate methods in tables by visit and treatment group. The change from baseline to endpoint (if necessary defined as the last

value carried forward) will also be described by summary statistics. Influenza-specific antibody titres (IgM, IgG, IgG1-4, haemagglutinin inhibition (HI) titre) will be analysed by calculating changes from the background pre-immune serum readings.

All individuals with at least one post-baseline measurement for efficacy will be included in the efficacy population. The analysis will include listings of objective response according to currently pertaining TGA influenza vaccine criteria, (e.g. seroconversion = four fold increase in HI over baseline, seroprotection = post-immunisation HI of 1:40 or greater; potency = fold increase in HI geometric mean titres (GMT). GMT and 95% confidence intervals will be estimated pre- and post-immunisation and compared across groups by ANOVA. The proportion of each vaccine group achieving seroconversion or seroprotection will be compared by Fisher's exact test.

An efficacy analysis to identify differences in treatment response between unadjuvanted and adjuvanted TIV groups and between needle and needless injector groups will be performed on the complete PPP irrespective of age. Additional subgroup efficacy analyses to identify significant differences in treatment response between unadjuvanted and adjuvanted TIV groups and between needle and needless injector groups will be performed stratifying subjects by age.

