### **5.2 Choice of control groups and blinding**

This is a randomized, controlled Phase 2 study. A total of up to 400 subjects will be recruited for the study, and randomly assigned on a one to one to one basis (1:1:1) to standard TIV, TIV + Advax 5mg or TIV + Advax 10mg. All subjects will also be randomised on a 1:1 basis to receive the immunisation via needle and syringe or Pharmajet needleless injector device. There will therefore be 6 subgroups in total.

As the vaccine containing Advax is a cloudy white colour whereas TIV is a clear solution, it is not possible for the staff administering the vaccine to be blinded. Subjects will be blinded and will not be informed which vaccine they receive. Similarly, where a trial adverse effect requires assessment, this will be performed by a blinded adjudicator. All laboratory tests will be performed blinded.

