### **9.8 Subgroup analyses**

A pooled efficacy analysis will be performed on the total study efficacy population. In addition, subgroup analyses of vaccine response rates will be performed stratifying responses according to the subject age and analysis of differences in GMT by ANOVA and seroconversion and seroprotection rates by Fishers exact test.

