### **9.10 Randomisation procedure**

Random allocation sequences will be generated by an independent source. . Randomisation codes will be held independently to the site. To randomise a subject the investigator or study co-ordinator will use an on-line interface to enter subject initials and date of birth. On entering this data, they will be issued with the next available randomisation code for the particular randomisation block or category to which the entered subject belongs, e.g. with or without Advax, 10mg or 20mg etc.

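### The tests named for GMT and response rates are unadjusted, so the formulation comparison forgoes precision that baseline titre, already collected, would give

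*Protocol*

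**What the plan says.** Protocol section 9.4 names the between-group tests. For titres, GMTs with their 95% confidence intervals are to be "estimated pre- and post-immunisation and compared across groups by ANOVA". For response rates: "The proportion of each vaccine group achieving seroconversion or seroprotection will be compared by Fisher's exact test". Section 9.8 carries the same pair into the age subgroups: "analysis of differences in GMT by ANOVA and seroconversion and seroprotection rates by Fishers exact test". No covariate, second factor or stratified form of either test is named.

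Baseline, device and age do appear elsewhere in the plan:

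- **Baseline.** Section 9.4 says titres, HI included, "will be analysed by calculating changes from the background pre-immune serum readings". It defines response as "seroconversion = four fold increase in HI over baseline, seroprotection = post-immunisation HI of 1:40 or greater" and potency as the fold rise in GMT. Section 9.2.2 admits to the per-protocol population only subjects with a baseline antibody value and a later one.
- **Device.** Section 5.2 crosses it with formulation: "All subjects will also be randomised on a 1:1 basis to receive the immunisation via needle and syringe or Pharmajet needleless injector device". Section 9.4 plans needle versus needleless as a separate efficacy comparison.
- **Age.** The main analysis takes all ages together; age-stratified analyses follow in sections 9.4 and 9.8.

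**The concern.** Pre-vaccination immunity is likely to vary widely. Section 6.1 admits any adult, section 6.2 excludes on vaccination history only those who have already had the 2012 vaccine, and section 8.7.1 records five years of vaccination history. When post-dose titre tracks baseline titre, a comparison that ignores baseline carries avoidable residual variance.

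Precision matters here for two reasons. Section 9.7 declines a power calculation and takes group size from a regulatory minimum. Section 1.1 asks whether the reduced adjuvant dose does as well as the higher one, a question answered by the width of an interval.

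This is also more than silence that a statistical analysis plan could fill. The protocol names the tests, and an analysis plan that follows it literally inherits the unadjusted forms.

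**Working it through.** **Group size.** Section 9.7 gives a minimum of 50 per group, 20% dropout and 65 per group. 50 / (1 − 0.20) = 62.5, rounded up to 63; the stated 65 leaves 65 × 0.8 = 52 evaluable. The plan's figure holds. Pooled over device, each formulation has 2 × 65 = 130 randomised and 130 × 0.8 = 104 evaluable.

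**Variance of the log-titre comparison.** Let ρ be the baseline-to-post correlation of log titre. The documents do not give it; 0.3 to 0.7 is assumed. With large samples, and equal SDs before and after vaccination:

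- ANCOVA relative to post-only ANOVA: 1 − ρ²
- change score relative to post-only ANOVA: 2(1 − ρ)
- ANCOVA relative to change score: (1 − ρ²) / [2(1 − ρ)] = (1 + ρ)/2

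| ρ | ANCOVA / post-only | Change / post-only | ANCOVA / change | 104 per arm is worth, against post-only |
|---|---|---|---|---|
| 0.3 | 0.91 (−9%) | 1.40 | 0.65 (−35%) | 104/0.91 = 114 |
| 0.5 | 0.75 (−25%) | 1.00 | 0.75 (−25%) | 104/0.75 = 139 |
| 0.7 | 0.51 (−49%) | 0.60 | 0.85 (−15%) | 104/0.51 = 204 |

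At ρ = 0.7 the ratio is 0.51, so the variance falls by 1 − 0.51 = 49%; 51% is the share that remains. The reduction against post-only ANOVA therefore runs from 9% to 49%.

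Both comparators are shown because section 9.4 does not settle which quantity the ANOVA tests. Its ANOVA sentence refers to GMTs before and after vaccination, another sentence refers to changes from pre-immune readings, and section 2.1 lists GMT increases as primary. ANCOVA is at least as precise as either.

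**Power for GMT.** Assumed: log10 SD 0.5, GMT ratio 1.5, two-sided 0.05, 104 per arm.

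| ρ | Post-only ANOVA | Change score | ANCOVA |
|---|---|---|---|
| 0.3 | 71.9% | 57.4% | 75.9% |
| 0.5 | 71.9% | 71.9% | 83.5% |
| 0.7 | 71.9% | 90.6% | 94.5% |

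At ρ = 0.5, ANCOVA moves power from 88.8% to 95.6% if the SD is 0.4, and from 56.2% to 68.6% if it is 0.6.

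**Response rates.** Two arms of 104 were simulated, 800 runs per setting, with the same SD and ratio. Baseline was centred on a titre of 20 and post-dose TIV on 60; titres were continuous. Power with Fisher's test, then with logistic regression on formulation and baseline log titre:

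| ρ | Seroprotection: Fisher, adjusted | Seroconversion: Fisher, adjusted |
|---|---|---|
| 0.3 | 44.4%, 52.2% | 36.0%, 50.7% |
| 0.5 | 41.4%, 53.2% | 42.6%, 58.0% |
| 0.7 | 40.1%, 59.9% | 66.8%, 76.5% |

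**Validity.** With no true difference, rejection rates were 3.8–4.6% for post-only ANOVA, 4.1–5.4% for change-score ANOVA, 2.8–5.1% for Fisher's test and 4.4–5.4% for adjusted logistic regression. The planned tests hold their level within simulation error. Some of the gap in the response-rate table reflects Fisher's conservatism rather than the covariate.

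**The case against.** The strongest reply is that section 9.3 calls the analysis descriptive, that this is a phase 2 study, that covariates are often left to an analysis plan, and that section 9.4 does not say one-way ANOVA, so a two-factor model is open to the sponsor. All of that stands, and it limits the point to an improvement. It does not remove it: Fisher's test has no covariate form, and no wording points to a baseline term in the ANOVA.

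Several stronger readings may tempt a reader, and the document does not support them:

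- **That baseline, device and age go unused.** Change from baseline, fold rise, seroconversion, the device comparison and the age strata all use them.
- **That the tests make the binary endpoints depend on baseline, or bias them.** The dependence comes from the four-fold and 1:40 definitions and remains under any test. Randomisation keeps the unadjusted comparison valid.
- **That seroprotection is diluted by subjects already at 1:40.** The share is not given, and adjustment leaves the raw difference in rates unchanged.
- **That the seroconversion rule fails for undetectable baselines.** The definition is given as an example of TGA criteria, and no detection limit is stated.
- **That randomisation had to be stratified by age.** Section 9.10 has staff "use an on-line interface to enter subject initials and date of birth" and issues codes by block or category, neither naming nor excluding age. Subgroup analysis does not require a stratum.
- **That every interval is too wide.** An adjusted odds ratio is conditional and its log-scale standard error need not be smaller; for the binary endpoints the gain is in power.

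**Conclusion.** The point holds as one of efficiency. The named tests of the primary immunogenicity endpoints omit a prognostic covariate that every subject in the efficacy analysis has, and a randomised factor. For log titre, the avoidable variance is 9% to 49% against post-only ANOVA and 35% to 15% against change scores, for an assumed ρ of 0.3 to 0.7 with equal SDs. The power figures rest further on an assumed SD and GMT ratio.

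The gain from device and age cannot be sized from the document. Device is balanced across formulations by the 1:1 crossing, so omitting it costs at most some residual variance. The change is worth making, but nothing in the planned analysis is invalid without it.

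**What to change.** In section 9.4, for each strain, replace the ANOVA with ANCOVA on log Day 28 HI titre with terms for formulation, device, baseline log titre and age (continuous). Report adjusted GMT ratios with 95% confidence intervals for each Advax dose versus TIV. This also settles which titre quantity is tested.

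Make the main comparison of seroconversion and seroprotection a logistic regression with the same terms. Keep the raw proportions and Fisher's test as supportive results, and leave the TGA endpoint definitions as they are.

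The cost is revised wording and slightly more analysis work; no extra subjects, samples or visits. Because the adjusted odds ratio is conditional, it should be shown beside the raw rates.
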